# Mothers and Babies Virtual Group (MBVG) for perinatal Latina women: study protocol for a hybrid type-1 effectiveness-implementation randomized controlled trial

**DOI:** 10.1186/s13063-024-08423-z

**Published:** 2024-09-11

**Keywords:** Postpartum depression, Prevention, Group intervention, Telehealth, Latina, Intervention

## Abstract

**Background:**

Immigrant Latinas (who are foreign-born but now reside in the USA) are at greater risk for developing postpartum depression than the general perinatal population, but many face barriers to treatment. To address these barriers, we adapted the Mothers and Babies Course—an evidence-based intervention for postpartum depression prevention—to a virtual group format. Additional adaptations are inclusion of tailored supplemental child health content and nutrition benefit assistance. We are partnering with Early Learning Centers (ELC) across the state of Maryland to deliver and test the adapted intervention.

**Methods:**

The design is a Hybrid Type I Effectiveness-Implementation Trial. A total of 300 participants will be individually randomized to immediate (*N* = 150) versus delayed (*N* = 150) receipt of the intervention, Mothers and Babies Virtual Group (MB-VG). The intervention will be delivered by trained Early Learning Center staff. The primary outcomes are depressive symptoms (measured via the Center for Epidemiologic Studies-Depression Scale), parenting self-efficacy (measured via the Parental Cognition and Conduct Towards the Infant Scale (PACOTIS) Parenting Self-Efficacy subscale), and parenting responsiveness (measured via the Maternal Infant Responsiveness Instrument) at 1-week, 3-month, and 6-month post-intervention. Depressive episodes (Structured Clinical Interview for DSM-V- Disorders Research Version) at 3-month and 6-month post-intervention will also be assessed. Secondary outcomes include social support, mood management, anxiety symptoms, perceived stress, food insecurity, and mental health stigma at 1-week, 3-month, and 6-month post-intervention. Exploratory child outcomes are dysregulation and school readiness at 6-month post-intervention. Intervention fidelity, feasibility, acceptability, and appropriateness will also be assessed guided by the Reach, Effectiveness, Adoption, Implementation, Maintenance (RE-AIM) framework.

**Discussion:**

This study will be one of the first to test the efficacy of a group-based virtual perinatal depression intervention with Latina immigrants, for whom stark disparities exist in access to health services. The hybrid effectiveness-implementation design will allow rigorous examination of barriers and facilitators to delivery of the intervention package (including supplemental components) which will provide important information on factors influencing intervention effectiveness and the scalability of intervention components in Early Learning Centers and other child-serving settings.

**Registration.:**

ClinicalTrials.gov NCT05873569.

**Supplementary Information:**

The online version contains supplementary material available at 10.1186/s13063-024-08423-z.

## Background

Between 10 and 22% of pregnant individuals in the USA develop postpartum depression (PPD) [1–4]. The effects of PPD extend across generations, with studies demonstrating that depressed mothers exhibit lower parenting self-efficacy [5, 6], less responsiveness to their child’s cues [7, 8] and less positive emotion [9] when engaging with their young children compared to non-depressed mothers. Immigrant Latinas (individuals who are foreign-born but now reside in the USA) represent a diverse population that has been shown to be at greater risk for developing PPD than the general perinatal population [10–13] due to a range of sociocultural and structural factors including acculturative stress, family separation, and high rates of trauma, poverty, and discrimination [10, 14]; perinatal is defined as pregnancy and the first year postpartum. However, despite elevated risk for PPD, immigrant Latinas have low rates of engagement with traditional mental health services due to a range of barriers (e.g., lack of insurance, competing demands, stigma) [15], suggesting the need to deliver interventions outside of traditional healthcare settings [16, 17].

Systematic reviews, including a 2019 United States Preventive Services Taskforce (USPSTF) review, highlight effective psychological interventions for preventing PPD onset and reducing depressive symptoms [18, 19]. The USPSTF recognized Mothers and Babies (MB), an intervention with content specific to the perinatal period built on cognitive-behavioral therapy (CBT) and attachment theory, as one of the two most efficacious interventions for preventing PPD. A series of randomized controlled trials (RCTs) demonstrate MB’s impact on reducing maternal depressive symptoms [20–23] and prevention of new cases of major depression [20, 21, 23]. MB was developed and tested via two RCTs with immigrant, Spanish-speaking Latinas [21, 23]. Low social support is a potent risk factor for PPD [24, 25], particularly salient among immigrant women [26, 27]. As such, several PPD preventive interventions—including MB—are delivered in a group format [18, 19]. Group preventive interventions targeting PPD [21, 23, 28] and other health conditions [29] have been well-received by immigrant Latinas [37, 38].

Despite evidence of effectiveness among immigrant Latinas, previous MB trials with Latinas have had several limitations, including variability in intervention dosage. In one trial [21], Latina participants averaged just over 50% attendance and greater intervention dosage was associated with increased effects on depressive symptoms; participants receiving > 50% of sessions had a − 0.53 effect size for reduction in depressive symptoms versus a − 0.28 effect size among all MB recipients.

EHealth interventions (delivered via telephone, apps, or web-based platforms) [30] mitigate several barriers to engaging perinatal immigrant Latinas in PPD interventions including transportation, childcare, and scarcity of language-concordant providers. Multiple reviews suggest that eHealth interventions demonstrate small to medium effect sizes in preventing or treating PPD [31, 32]. The COVID-19 pandemic required a transition from in-person to virtual interventions with early reports of success including among group interventions delivered virtually to immigrant adults with limited English proficiency [33]. There is evidence for the acceptability of a range of eHealth approaches and of increasing internet use among immigrant Latinos [29, 34, 35]. Virtual interventions can also address system-level barriers by promoting efficient use of bilingual staff [36, 37]. Previous studies have found high satisfaction and engagement with *virtua*l group interventions among immigrant Latinas for a range of conditions, including diabetes [38] and cancer [39, 40]. However, despite acceptability of virtual group interventions among Latinas [40] and the advantage of a virtual group modality to mitigate both risks for PPD and barriers to engagement among immigrant Latinas, few prior studies have examined the use of a virtual group-based preventive intervention for PPD with this population.

### MB adaptation for virtual group delivery

To address gaps in PPD preventive intervention delivery to immigrant Latinas, our team recently completed a pilot study in which we delivered MB virtually via Zoom: Mothers and Babies Virtual Group (MB-VG) [41]. MB-VG was developed in close collaboration alongside key community partners (e.g., service providers). While retaining key intervention components, we made four main modifications to the in-person MB group intervention. *First*, MB-VG’s delivery was changed from six sessions each lasting 90–120 min to 10 sessions each lasting ~ 60–75 min. Given the variability in dosage found in previous MB trials with immigrant Latinas, as well as practical barriers (e.g., childcare), partners believed shorter sessions would be more acceptable and feasible. *Second*, MB-VG added a “Resource Advocate” to facilitate participants’ connection to nutrition support, directly addressing food insecurity—a key social determinant of health associated with PPD among immigrant Latinas [42], and barriers to enrollment in nutrition assistance programs such as the Supplemental Nutrition Assistance Program (SNAP) [43]. Resource Advocates are rigorously trained Spanish/English bilingual undergraduate students supervised by medical school faculty and staff [44]. *Third,* due to partners’ desire for additional child health and development-focused guidance around topics including infant growth, development, and behavior, we incorporated a pediatric health care provider into sessions, with the provider joining virtual session for 15 min at the conclusion of the core MB content (see Table 1 for outline of content delivered by pediatric health care provider, for which a session-by-session manual was also developed). *Fourth*, MB-VG includes text messaging to promote session attendance, encourage skill practice, and reinforce health-related content delivered by the pediatric health care provider. We will send text messages 24–72 h apart via the HealthySMS system, a web-based platform used to deploy text messages in previous MB studies [45] and other studies of mental health interventions [46, 47].

**Table 1 Tab1:** MB-VG content, by intervention session

MB m odule	MB session	Core MB content found in session (Each session reinforced with text messages)	Pediatrician topics
**Introductory**	**1**	Introduction to MB-VG	Introduction to Pediatrician & Resource Advocate and an overview of SNAP benefits
**Pleasant** **Activities**	**2**	Pleasant activities and my mood	Nutrition: Healthy Infant Feeding
	**3**	Pleasant activities and your baby	Development: Promoting Language Development
**Thoughts**	**4**	Thoughts and how they affect our mood	Development: Soothing a Crying Baby
	**5**	Identifying and modifying unhelpful thoughts	Nutrition: “Milk” choices
	**6**	Relationship between mood, thoughts, and future; promoting child’s healthy thinking	Nutrition: Health Infant Growth
**Contact** **With Others**	**7**	Contact with other people and my mood	Development: Teaching Boundaries
	**8**	Social support network for mother and child	Nutrition: Beverage Options
	**9**	Communication style and mood; role transitions with new child in home	Development: Promoting bilingualism
**Review**	**10**	Review and planning for the future	Wrap Up: Transition to Pediatrician

## Methods/design

### Study aims and hypotheses

Aim 1: To examine MB-VG effectiveness with perinatal immigrant Latinas at risk of PPD. Women receiving MB-VG will exhibit greater reductions in depressive symptoms (Hypothesis 1), exhibit fewer cases of PPD (H2) and report increased parenting self-efficacy and responsiveness (H3) compared to control participants receiving usual family support services. Exploratory Aim: Among enrolled participants (*n* ~ 150) who have an older child aged 2.5–4.5 years, we will examine whether the skills taught in MB-VG also promote less child dysregulation and greater child readiness for school. Aim 2. To evaluate MB-VG implementation. To inform future intervention delivery and scalability, we will assess key implementation outcomes. Guided by the Reach, Effectiveness, Adoption, Implementation, Maintenance (RE-AIM) framework [48], we will use mixed methods (e.g., semi-structured interviews, survey data, and session audio-recordings) to assess MB-VG reach, adoption, implementation, and maintenance. Aim 3. To examine contextual factors influencing MB-VG effectiveness and implementation. Guided by the Consolidated Framework for Implementation Research (CFIR) [49], we will measure contextual factors at the outer, inner, actors, intervention, and implementation process (virtual) levels via mixed methods. Publications will be developed for each study aim, with authorship determined in accordance with ICMJE guidelines. SPIRIT reporting guidelines are used in this manuscript [50].

### Setting: Maryland’s Judy Centers

Enacted in 2000 by the Maryland State Legislature, Judith P. Hoyer Early Learning Hubs (“Judy Centers”) are a network of center-based early childhood programs aimed at promoting kindergarten readiness of children from low-income families [51]. There are currently 85 Judy Centers with a major expansion planned over the next decade. Along with providing core services (e.g., case management, developmental assessments, parenting support), Judy Center partners work with and make referrals to local external agencies*.*

### Study design

This is a Hybrid Type 1 Implementation-Effectiveness trial designed as a two-arm randomized controlled trial (RCT), with individuals randomized (using REDCap-generated random numbers) via 1:1 allocation ratio to MB-VG or usual Judy Center services followed by delayed intervention receipt (receipt after data collection at 6-month time point). We selected an RCT design given our primary study aim to examine effectiveness of the MB-VG intervention. Women randomized to the usual care arm will be offered participation in MB-VG after completing their final data collection activity at 6 months post-randomization. We recognize this may result in MB-VG being offered beyond the period where there is greatest prevalence of depression among new mothers; however, this approach was endorsed by Judy Center partners. Specifically, they felt that in its absence some women may not consent to participation knowing they may not be able to receive MB-VG.

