### Study intervention

#### MB-VG

Women randomized to the MB-VG arm will begin to receive the 10-session MB-VG intervention within 1 month of enrollment. These sessions are delivered weekly over a maximum of 15 weeks, with each session lasting between 60 and 75 min. All MB-VG groups will be delivered in Spanish by a trained MB-VG facilitator. Prior to each session, a member of the research team will test Zoom connections with each participant. Each session consists of cognitive-behavioral therapy-based content and is comprised of didactic and interactive content and ends with a “personal project” that encourages clients to practice using the core skills they learned in the session (see Table 1 below for core content found in each MB-VG session). In addition, a pediatrician will provide content related to nutrition, parenting, and child development. Text messages will be used as an implementation strategy to promote session attendance, encourage skill practice, and reinforce pediatrician content. Two bilingual Judy Center staff will co-facilitate each MB-VG intervention cohort. Based on previous MB research, attendance at over 50% of intervention sessions is defined as “full-dosage”; therefore, for this study, receipt of ≥ 6 sessions will constitute full-dose of MB-VG. We will document attendance at intervention sessions by asking one of the intervention co-facilitators to complete an attendance log for each MB-VG session. A member of the research team will also use Zoom login information to confirm the information found in the attendance logs. Participants who do not attend a session will receive a brief link via text to a video that reviews the session topics and key points. All videos for missed session are approximately 5 min or less.

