#### Usual care

Women randomized to the usual family support services/usual care arm will receive Judy Center services without any MB-VG intervention during the study period (but will receive MB-VG after 6 months via our delayed intervention design, if interested). Judy Centers provide an array of services including parenting education, case management, family health and developmental assessments and referrals, and partnerships with childcare and education providers (e.g., Head Start).

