### Self-report surveys

All participants will be asked to complete surveys at four time points: baseline (pre-intervention), 1-week post-intervention, 3 months post-intervention, and 6 months post-intervention to assess primary and secondary outcomes, as well as acceptability and feasibility. Data will be collected online and managed via REDCap. To minimize potential literacy issues, we will use REDCap’s text-to-speech function to allow participants to listen to audio survey questions if they prefer. For participants who strongly prefer to have a research team member administer surveys, a bilingual research assistant will conduct surveys by phone. We anticipate each survey will take 40–60 min, with participants remunerated $25–40 per survey, depending on the time point.

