### Structured clinical interviews

To assess onset of major depression, all participants will be asked to complete the Mood Disorders module of the Structured Clinical Interview for DSM-V Diagnosis, Research version (SCID-5-RV) [85], a semi-structured interview for DSM-V Axis I diagnoses. The SCID will be administered at the 3- and 6-month post-intervention time points. Participants will be compensated $25 for completing the clinical interview at 3-month, and $30 for completing a clinical interview at 6-month post-intervention.

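### The usual-care arm's last data collection is dated 6 months post-randomization, but every participant's last assessment is dated 6 months post-intervention, roughly 2 to 4.5 months later

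*Protocol article*

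**What the plan says.** All references are to the protocol article.

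- **Study design**, on the usual-care arm: "Women randomized to the usual care arm will be offered participation in MB-VG after completing their final data collection activity at 6 months post-randomization". An earlier sentence of the same section gives the order without an origin for the 6 months: "usual Judy Center services followed by delayed intervention receipt (receipt after data collection at 6-month time point".
- **Usual care**: controls "will receive MB-VG after 6 months via our delayed intervention design, if interested". Again no origin is given. The same sentence says they get no MB-VG during the study period.
- **Self-report surveys**: all participants are surveyed at "baseline (pre-intervention), 1-week post-intervention, 3 months post-intervention, and 6 months post-intervention to assess primary and secondary outcomes".
- **Structured clinical interviews**: "The SCID will be administered at the 3- and 6-month post-intervention time points", and all participants are to be interviewed.
- **Virtual observations**, the **Table 2** footnote and the **Abstract** also place the last assessment at 6 months post-intervention.
- **MB-VG**: women in the intervention arm "will begin to receive the 10-session MB-VG intervention within 1 month of enrollment", and "These sessions are delivered weekly over a maximum of 15 weeks".
- **Statistical analysis, Effectiveness outcomes**: the primary analyses take each follow-up time separately, adjusting for the pretest measure.

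**The concern.** The article uses two clocks. Outcome visits run from the end of the intervention. The only explicit date for the control arm's final data collection runs from randomization. The two cannot coincide, because the start delay and the course of sessions lie between randomization and the end of the intervention.

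Staff who schedule from the Study design section would see controls for the last time well before staff who schedule from the survey and interview sections. Because randomization balances infant age at entry, any arm difference in time since randomization becomes the same difference in infant age at assessment. The SCID is used to assess onset of major depression, so a shorter follow-up in one arm also means less time for an episode to occur there.

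The 6-month contrast has no cushion, since each follow-up is analysed on its own. By Table 2, the SCID is collected only at 3 and 6 months, and the observed parenting measure (PCOS), the DB-DOS and the school readiness measure only at 6 months.

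**Working it through.** **Inputs**

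- Start delay *s*: 0 to 1 month after enrollment (MB-VG section).
- Course length *L*: 10 weekly sessions, so 9 weeks from first to tenth session, or 10 if counted as full weeks; 15 weeks at most (MB-VG section).
- Last assessment: 6 months after the intervention ends (Self-report surveys, Structured clinical interviews, Virtual observations, Table 2, Abstract).
- Control arm's final data collection: 6 months after randomization (Study design).
- Assumption: enrollment and randomization fall at about the same time.
- Weeks per month: 365.25 / 12 / 7 = 4.348.

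**Formulas** (months from randomization)

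- End of intervention: E = s + L / 4.348
- 3-month visit: E + 3
- 6-month visit: E + 6
- Gap between the two dates for the final visit: (E + 6) − 6 = E
- Where a control visit at 6 months post-randomization sits on the MB-VG arm's post-intervention clock: 6 − E

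**Can the stated 6 months be reproduced?** That needs E = 0, meaning no start delay and no sessions. The smallest E the article allows is 0 + 9 / 4.348 = 2.07. No permitted combination gives 6 months.

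**Results**

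| Start delay (months) | Course (weeks) | E = gap | 3-month visit | 6-month visit | 6 − E |
|---|---|---|---|---|---|
| 0 | 9 | 2.07 | 5.07 | 8.07 | 3.93 |
| 0 | 10 | 2.30 | 5.30 | 8.30 | 3.70 |
| 0 | 15 | 3.45 | 6.45 | 9.45 | 2.55 |
| 1 | 9 | 3.07 | 6.07 | 9.07 | 2.93 |
| 1 | 10 | 3.30 | 6.30 | 9.30 | 2.70 |
| 1 | 15 | 4.45 | 7.45 | 10.45 | 1.55 |

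The MB-VG arm's 6-month visit falls 8.07 to 10.45 months after randomization. A control visit at 6 months post-randomization falls 2.07 to 4.45 months before that, at the equivalent of 1.55 to 3.93 months post-intervention. On time since randomization it lines up with the MB-VG arm's 3-month visit (5.07 to 7.45 months), not with its 6-month visit.

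**The case against.** **A slip of one word.** A single phrase in Study design stands against the Abstract, the Table 2 footnote and three measures sections, two of which cover all participants explicitly. Post-randomization may simply have been written for post-intervention, with control visits dated from the matching MB-VG cohort. In that case the arms are measured together and no bias arises. This stands as a real possibility, and it is why the bias is stated conditionally. It does not remove the contradiction: the phrase is the only explicit date given for the control arm's final visit.

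**Material not shown.** The schedule figure is not available, and an article may leave the rule for dating control visits to the full protocol. That is fair, so the lack of such a rule is not counted here as a fault in itself. The fault is a stated date that conflicts with other stated dates, and a figure would not reconcile the two texts.

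**A stronger reading that fails.** A reader might infer that controls are opened to MB-VG at 6 months post-randomization while still awaiting their last assessment, so that crossover dilutes the 6-month and even the 3-month contrast. The documents do not support this. Both Study design sentences place the offer after the final data collection, and Usual care excludes MB-VG during the study period. Getting crossover requires keeping the date in the quoted sentence and discarding its condition. Nor is there a basis for claiming bias at 3 months, since that sentence dates only the final visit.

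**Prevalence over time.** Study design says only that the delayed offer may come after the period of greatest depression prevalence. It gives no rates for months 6 to 10, so neither the size nor the direction of any bias can be derived from the article.

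**Conclusion.** The contradiction is in the current text and needs correcting. The two dates for the control arm's last assessment differ by 2.07 to 4.45 months, given a start within 1 month, 9 to 15 weeks of sessions, and enrollment at about the time of randomization.

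What follows depends on which text is operative:

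- **Study design followed literally:** the 6-month CES-D, SCID, parenting and child contrasts confound arm with time since randomization and child age, and the arms have unequal time at risk for SCID onset. Adjusting for the pretest measure does not repair timing that is tied to arm.
- **Post-randomization a slip for post-intervention, with controls dated from the matching cohort:** no bias, only wrong wording.

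The article does not show which applies. The point concerns the 6-month contrast only.

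**What to change.** Reconcile the Study design sentence with the MB-VG section, the Table 2 footnote and the sections on surveys, interviews and observations. Specifically:

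1. Name one time origin for follow-up visits in both arms, for example randomization, or the start or end date of the concurrent MB-VG cohort, and apply the same windows to both arms.
2. Express the control arm's final data collection on that clock, so that it still precedes the offer of MB-VG as Study design intends.
3. Give the origin wherever the article says only 6 months (the earlier Study design sentence and Usual care).

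The article expects recruitment to run from September 2023 to September 2025, so some visits may already have been scheduled. Reporting actual time since randomization at each visit, by arm, would show which rule was used.

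The cost is protocol wording and a visit-date rule in REDCap, with no added participants or procedures. If control visits are now scheduled from randomization, some will move later, and the offer of MB-VG that follows them will move with them. If the phrase is only a slip, nothing moves.
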